### Involvement of external parties

Psychiatric staff who were involved in validating the Chinese version of the CIS-R in Hong Kong were consulted regarding the telephone diagnostic interview training, item selection, and ICD-10 scoring algorithm. Clinical psychologists specialized in sleep disorders and potential end-users were invited by the research team to provide feedback regarding the study design (e.g., the measures, recruitment strategies, Facebook page), as well as proACT-S revamp and beta testing.

### Possible harms

Adverse events, such as increased suicidal risk and hospital admission, study attrition rates, and significant deterioration in primary outcomes, are monitored and recorded throughout the study trial. Treatment discontinuation decision may be made at the discretion of the principal investigator, for reasons concerning participants’ safety. The proportion of participants experiencing any adverse events in each group will be reported in the results of this RCT study.

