## Methods

### Trial design

This is a two-arm, with equal randomization (1:1 allocation ratio) parallel, superiority RCT. It compares a self-help smartphone-based CBT-I intervention to a waitlist control condition. The self-help treatment is delivered through “proACT-S,” a smartphone application developed by the corresponding author’s research team. The results from a pilot study showed that proACT-S was efficacious for treating insomnia and was positively received by the users [23]. The current RCT is designed to test the efficacy of proACT-S in treating people with MDD and insomnia. Participants’ change in depressive and insomnia symptoms after the CBT-I intervention will be compared with that of the waitlist control group. The rationale for choosing waitlist control as the comparison condition is twofold: (1) it allows researchers to determine the effect of the intervention against not receiving treatment during the trial period and (2) it ensures that all participants will eventually receive the treatment.

Prior to trial entry, participants complete a two-stage screening. Their eligibility is assessed by an online survey, followed by a telephone diagnostic interview. After the two-stage screening, the assessments, randomization, and intervention are carried out via proACT-S. The research design is summarized in Fig. 1. The full SPIRIT checklist is provided as Additional file 1.

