#### Withdrawal criteria

Participants are withdrawn if, during the main study trial, they (1) have concurrent psychological treatment at least once per month; or (2) are taking prescribed psychiatric drugs such as antidepressants, tranquilizers, sleeping pills regularly; or (3) are being diagnosed with psychosis or schizophrenia; or (4) are participating in any other academic studies or clinical trials related to insomnia and/or depression; or (5) have suicidal ideations defined as scoring ≥ 2 on the BDI-II suicidal ideation item; or (6) have experienced serious diseases, significant life events, hospitalization, or fatalities; or (7) withdraw their consent; or (8) do not complete each assessment within 2 weeks, do not submit consent within 2 weeks after proACT-S personal account registration, or do not log into proACT-S within 2 weeks after random group assignment. In addition, participants in the waitlist control group who fail the cross-condition contamination check are withdrawn. Participants in the waitlist control group are withdrawn if (1) they have viewed part or all treatment module content as shown by people who are undergoing this study’s treatment or who have completed this study’s treatment, or who are very familiar with proACT-S (except the proACT-S project team), or (2) they have watched part or all of the treatment module videos included in proACT-S, or (3) they have completed part or all of the treatment module homework in proACT-S.

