**Assessments:**								
*Primary outcome measures*		CBT-I	WLC		CBT-I	WLC	CBT-I	WLC
Depression severity (CES-D)		X	X		X	X	X	X
Insomnia severity (ISI)		X	X		X	X	X	X
Sleep quality (PSQI)		X	X		X	X	X	X
*Secondary outcome measures*		CBT-I	WLC		CBT-I	WLC	CBT-I	WLC
Subjective health (SF-12 Version 1)		X	X		X	X	X	X
Anxiety (HADS-A)		X	X		X	X	X	X
Treatment expectancy (modified CEQ)		X	X		X			X
Treatment acceptability (modified PARS)		X	X		X			X
Demographics	X							
Clinical comorbidity	X							
*Post-screening eligibility assessments*		CBT-I	WLC		CBT-I	WLC	CBT-I	WLC
Withdrawal criteria					X	X	X	X
Cross-condition contamination check						X		X

*CES-D* Center for Epidemiologic Studies Depression Scale, *ISI* Insomnia Severity Index, *PSQI* Pittsburgh Sleep Quality Index, *HADS-A* Hospital Anxiety and Depression Scale—Anxiety subscale, *CEQ* Credibility/Expectancy Questionnaire, *PARS* Participant Acceptability/Usability Rating Scale

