### Participant timeline

Individuals interested in participating are invited to complete a two-stage screening. In stage 1 online rapid screening, they complete an online survey to review their eligibility. Those who have passed the online rapid screening will receive a link within the Qualtrics platform to sign up for the stage 2 telephone diagnostic interview screening. These telephone interviews are conducted by project assistants, who have been trained and supervised on the administration of the modified Chinese version of the CIS-R [34].

Individuals who do not meet the stage 2 telephone diagnostic interview screening eligibility criteria will receive a list of references related to insomnia and depression produced by the Department of Health and the Social Welfare Department under the Government of the Hong Kong SAR. Information regarding crisis hotlines and integrated community centers for mental wellness are provided to those currently with suicidal plans or acts, or those who have had suicidal plans or acts within the past 12 months.

Individuals who have passed the two-stage screening are directed to download proACT-S either from App Store or Google Play. Eligible participants are guided to register for their own personal accounts to enter the main study trial. They then complete the baseline assessment via proACT-S. After that, they are randomly assigned in a 1:1 ratio either to CBT-I condition or waitlist control condition.

Participants in the CBT-I condition start the 6-week CBT-I immediately after randomization, complete the post-intervention assessment right after they finish the treatment, and complete the follow-up assessment 6 weeks after the post-intervention assessment. Participants in the waitlist control group wait for 6 weeks without the proACT-S intervention and then complete the post-intervention assessment 6 weeks after the baseline assessment. The waitlist control participants start CBT-I (equivalent to that of the CBT-I group) immediately after completing the post-intervention assessment, and they complete the follow-up assessment right after finishing the 6-week CBT-I.

Emails and WhatsApp reminders are sent to participants to increase their engagement and to enhance treatment compliance. Upon completion of the study, each eligible participant receive cash coupons of HKD $100 as a token of appreciation for their participation. The proposed flow of participants is displayed in Fig. 2.

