### Blinding

The principal investigator is blind to both the outcome assessment and group assignment. The research team is blind to the outcome assessment because all three assessments are self-reported and carried out via the smartphone app, but is not blind to the group assignment as research members need to send emails and WhatsApp reminders to the participants to enhance treatment compliance. Efforts are made to minimize participants’ knowledge of treatment allocation by informing participants that the treatment start date is randomly assigned. Statistical analyses will be carried out by a researcher blind to the study protocol. In the unlikely event of a critical incident, the research team, as well as the principal investigator, will be authorized to break the blind and carefully record it on the Case Report Form.

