### Data analysis plan

The principle of intention-to-treat analysis will be adopted, in which all randomized participants with missing observations, from lost to follow-up or incomplete outcome assessments, will be handled by multiple imputation [53]. Missing data is assumed to be 5%.

Chi-square tests and independent *t* tests will be conducted to examine if participants in the CBT-I and waitlist control conditions differ in terms of demographic characteristics, clinical comorbidity, and baseline outcome scores. Multilevel linear mixed model based on the intention-to-treat principle will be used to calculate between-condition mean differences in the primary outcome changes in sleep quality, insomnia, and depression severity from baseline to post-intervention assessments. Multilevel linear mixed model based on the intention-to-treat principle will also be used to analyze secondary outcomes of the baseline to post-intervention change in subjective health and anxiety between CBT-I and waitlist control conditions. Clustering effect, significant baseline differences in demographics, clinical characteristics, and outcome variables will be adjusted for. Pair-sample *t* tests based on the intention-to-treat principle will be used to analyze changes in primary outcomes, subjective health, and anxiety obtained at post-intervention and 6-week follow-up separately for each condition. All comparisons are planned with a 5% two-sided significance level. Bonferroni adjustment will be applied.

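### The per-group any-adverse-event proportion has no stated period except the whole trial, in which the waitlist also receives CBT-I

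*Protocol article*

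**What the plan says.** Under Possible harms, the protocol article lists increased suicidal risk, hospital admission and significant worsening of the primary outcomes among its adverse events. It says that these "are monitored and recorded throughout the study trial". A later sentence in the same section gives the planned summary: "The proportion of participants experiencing any adverse events in each group will be reported in the results of this RCT study". That sentence carries no period of its own.

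Participant timeline describes the crossover: "The waitlist control participants start CBT-I (equivalent to that of the CBT-I group) immediately after completing the post-intervention assessment". The waitlist's follow-up assessment comes when that six-week course ends. The CBT-I arm has its follow-up assessment six weeks after its post-intervention assessment. Table 2 places post-intervention at week 7 and follow-up at week 13 for both arms.

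Trial design gives as one reason for the waitlist that "it allows researchers to determine the effect of the intervention against not receiving treatment during the trial period". The Data analysis plan states a window for the efficacy contrast: "between-condition mean differences in the primary outcome changes in sleep quality, insomnia, and depression severity from baseline to post-intervention assessments". It analyses later change separately within each condition.

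**The concern.** From the post-intervention assessment onward there is no untreated group. A cumulative proportion over the whole trial counts the waitlist's events on CBT-I as control-arm events. It therefore contrasts early with late treatment, while the waitlist was chosen to show treatment against none. The article stops its between-condition efficacy comparison before the crossover but states no such limit for harms.

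At stake is the reader's view of safety in people with major depression. Extra events on CBT-I could look smaller than they are or vanish, and so could events that CBT-I prevents.

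**Working it through.** **Inputs.** The article gives no adverse event rate, so there is no harms figure to reproduce. From Sample size: 199 participants before attrition, 30% attrition, and 199/0.7 = 284.3, rounded up to 285, or 142.5 per arm. Everything else is assumed:

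- t, u: risk of at least one event per six weeks on and off CBT-I.
- r: share retained into the second six weeks, equal in both arms and independent of events. r = 0.7 if the full 30% is lost by post-intervention.
- c: share of the difference t − u that persists in the CBT-I arm after treatment, so its later risk is w = u + c(t − u).

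**Formulas.**

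- Randomised period: difference = t − u.
- Whole trial, CBT-I arm: 1 − (1 − t)(1 − r·w).
- Whole trial, waitlist: 1 − (1 − u)(1 − r·t).
- Whole-trial difference: (t − u)[1 − r + r·c·(1 − t)].

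Only a first event counts towards any event, so withdrawing people after an event does not alter these expressions.

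**No persistence (c = 0).** The fraction kept is 1 − r at any event rate: 0% at r = 1, 20% at r = 0.8, 30% at r = 0.7.

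**Worked case, t = 0.08, u = 0.04, r = 0.7.**

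- c = 0: CBT-I 1 − 0.92 × 0.972 = 0.1058; waitlist 1 − 0.96 × 0.944 = 0.0938; difference 0.0120.
- c = 0.5: w = 0.06; CBT-I 1 − 0.92 × 0.958 = 0.1186; difference 0.0249.
- c = 1: w = 0.08; CBT-I 1 − 0.92 × 0.944 = 0.1315; difference 0.0378.

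**Range at r = 0.7** (percentage points, fraction kept in brackets):

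| t v u | Randomised period | c = 0 | c = 0.5 | c = 1 |
|---|---|---|---|---|
| 8% v 4% | +4.0 | +1.2 (30.0%) | +2.5 (62.2%) | +3.8 (94.4%) |
| 4% v 8% | −4.0 | −1.2 (30.0%) | −2.5 (63.6%) | −3.9 (97.2%) |
| 20% v 10% | +10.0 | +3.0 (30.0%) | +5.8 (58.0%) | +8.6 (86.0%) |

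**Full retention (r = 1), t = 0.15, u = 0.05.** The 10-point difference becomes 0, 4.25 or 8.5 points for c = 0, 0.5 and 1. If the CBT-I arm's later risk fell below the untreated level, to 2.5%, the sign would reverse: (1 − 0.15)(0.025 − 0.05) = −2.1 points.

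**The case against.** The strongest reply is that nothing in Possible harms is wrong. Recording events for the whole trial is right, and reporting a proportion per group is standard. The period is attached to recording, and the reporting sentence stands apart from it. A reader might infer that the article commits to a whole-trial proportion. It does not: reporting by period is not ruled out, and the full protocol or an analysis plan could set a window. This stands, and it limits the point to what follows from the natural reading.

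The consequence is also small. The figure has no test or stopping rule attached. Worsening of the primary outcomes, one of the listed harms, is also reflected in the between-condition comparison up to post-intervention. This stands too, although a comparison of mean change does not show the proportion harmed.

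Full disclosure over the whole study is a legitimate aim. The fix below keeps it.

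A reader might also see a further risk in the Blinding section: "Statistical analyses will be carried out by a researcher blind to the study protocol". That does not support the point. The article does not assign the harms table to that researcher, and blinding says nothing about how events are tabulated.

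What does not fall away is that the section fixes a specific summary, the only period beside it spans the crossover, and the article does state a window for efficacy.

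**Conclusion.** The point holds as a minor, cheap improvement. If the proportion is cumulated over the only period that the section names, it compares immediate with delayed CBT-I and can shrink or hide a difference from no treatment in either direction.

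The size is unknown. Under the assumptions above, with c between 0 and 1, the loss runs from total (full retention, no persistence) to almost none (97% kept). A reader might infer that harm from CBT-I will in fact be concealed, or that the summary favours the app. The documents support neither, because they give no event rates and the dilution works equally against a protective effect. Sample size and efficacy conclusions are unaffected.

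**What to change.** In Possible harms, define the between-group any-adverse-event proportion over the randomised period only. Use the same length of time in both arms and end it before the waitlist starts CBT-I, for example weeks 1 to 7 of Table 2. Report later events separately by arm, labelled as on CBT-I for the waitlist and after treatment for the CBT-I arm.

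A fixed length is safer than running from allocation to each participant's post-intervention assessment. The Allocation section randomises one week after baseline, and Participant timeline puts the waitlist's post-intervention assessment six weeks after baseline, against week 7 in Table 2. Taken literally, the waitlist would have 6 − 1 = 5 weeks from allocation, while the CBT-I arm has a six-week course. If the waitlist did start CBT-I at week 6, the window should end there in both arms.

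The cost is mainly wording. The "Withdrawal criteria" row of Table 2 already schedules a check at post-intervention and follow-up in both arms. It covers hospitalisation and those who "have suicidal ideations defined as scoring" 2 or more on the BDI-II item. The primary outcomes are measured at both points. Other events need a recorded date.

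The main table will hold fewer events. With 8% v 4%, 142.5 per arm, r = 0.7 and no persistence, about 17 participants have an event in the randomised period (11.4 + 5.7 = 17.1), against about 28 over the whole trial (15.1 + 13.4, or 28.4 before rounding).

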### Data analysis plan

The principle of intention-to-treat analysis will be adopted, in which all randomized participants with missing observations, from lost to follow-up or incomplete outcome assessments, will be handled by multiple imputation [53]. Missing data is assumed to be 5%.

Chi-square tests and independent *t* tests will be conducted to examine if participants in the CBT-I and waitlist control conditions differ in terms of demographic characteristics, clinical comorbidity, and baseline outcome scores. Multilevel linear mixed model based on the intention-to-treat principle will be used to calculate between-condition mean differences in the primary outcome changes in sleep quality, insomnia, and depression severity from baseline to post-intervention assessments. Multilevel linear mixed model based on the intention-to-treat principle will also be used to analyze secondary outcomes of the baseline to post-intervention change in subjective health and anxiety between CBT-I and waitlist control conditions. Clustering effect, significant baseline differences in demographics, clinical characteristics, and outcome variables will be adjusted for. Pair-sample *t* tests based on the intention-to-treat principle will be used to analyze changes in primary outcomes, subjective health, and anxiety obtained at post-intervention and 6-week follow-up separately for each condition. All comparisons are planned with a 5% two-sided significance level. Bonferroni adjustment will be applied.

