### Sample size

The most updated meta-analysis of 28 self-help CBT-I RCTs [19] showed a significant treatment effect in alleviating depressive symptoms (Hedges’ *g* = 0.35) and insomnia symptoms (Hedges’ *g* = 0.79). It also found that the mean cumulative study attrition rates were 21.25% (SD = 15.31%) and 18.4% (SD = 18.21%) in the treatment and the waiting list/routine care/no treatment/psychoeducation groups, respectively. Hence, a conservative small effect size (Cohen’s *f* = 0.2) and an attrition rate of 30% are estimated for the present study.

The sample size calculation for each of the three primary outcomes (i.e., insomnia severity, poor sleep quality, and depression severity) is based on mixed ANCOVA using GPower 3.1. To conduct a 2 (condition: CBT-I versus waitlist control) × 2 (assessment: baseline versus post-intervention) mixed ANCOVA with an alpha value set at 0.05, two-sided, 80% power to detect a small effect of 0.2 (Cohen’s *f*) between two groups while controlling for 12 covariates (demographics, clinical comorbidity, treatment expectancy, and acceptability of treatment), a total sample size of 199 will be required. In order to account for 30% attrition, a total sample of 285 participants will be sufficient to detect a small effect size (Cohen’s *f* = 0.2) for the difference in the change in each of the three primary outcomes (i.e., insomnia severity, poor sleep quality, and depression severity) from baseline to post-intervention between CBT-I condition and waitlist control condition with a two-sided 5% significance level and a power of 80%.

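### Covariates in the primary model, including the baseline outcome, are chosen by baseline significance tests, and the sample-size section assumes a different, fixed set with expectancy and acceptability at an unstated time point

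*Protocol article*

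**What the plan says.** **Data analysis plan.** Chi-square and independent t tests are planned to see whether the arms "differ in terms of demographic characteristics, clinical comorbidity, and baseline outcome scores". The primary analysis is a multilevel linear mixed model for "between-condition mean differences in the primary outcome changes in sleep quality, insomnia, and depression severity from baseline to post-intervention assessments". The covariate rule is: "Clustering effect, significant baseline differences in demographics, clinical characteristics, and outcome variables will be adjusted for".

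**Allocation.** Randomisation is simple, 1:1 and automated.

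**Sample size.** The calculation is for a 2 × 2 mixed ANCOVA on each of the same three primary outcomes over the same interval, "controlling for 12 covariates (demographics, clinical comorbidity, treatment expectancy, and acceptability of treatment), a total sample size of 199 will be required". The 12 are not itemised and no measurement time is given for them.

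**Acceptability of treatment, and Abstract.** The acceptability scale records how participants evaluate the treatment delivered by the app. Expectancy and acceptability are both secondary outcomes.

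**Table 2.** The rows for expectancy and for "Treatment acceptability (modified PARS" carry the same marks: baseline in both arms, post-intervention in CBT-I only, 6-week follow-up in waitlist only.

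**The concern.** The covariate rule is a positive statement, not a detail left for a later document. Under correct simple randomisation the null hypothesis of each baseline test is true by construction, so a significant result identifies a chance imbalance and not a variable that predicts outcome. A strongly prognostic variable that happens to be balanced is left out of the covariate set. A weak one that happens to be unbalanced is put in. The content of the primary model then varies from one realisation of the trial to the next.

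The baseline value of the outcome falls under the same rule, although it would usually be the most useful covariate and is already collected from everyone.

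The Sample size section does not resolve this. Its set is unconditional, has no baseline outcome, and contains two measures that the analysis rule does not mention. At stake are power, a primary model that is known before the data are seen, and the possibility that a measure affected by treatment enters the between-arm comparison.

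**Working it through.** **1. Reproduce the plan's figure.** Inputs from Sample size: f = 0.2, alpha 0.05 two-sided, power 80%, 12 covariates, 30% attrition. F test with numerator df 1, denominator df N − 2 − 12 and noncentrality f²N = 0.04N:
- N = 198: power 0.7994
- N = 199: power 0.8014, so 199 is the smallest sufficient N
- 199 / 0.7 = 284.3, rounded up to 285

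Both figures reproduce. Repeating this with between 0 and 20 covariates always gives 199, because only the denominator df moves (power 0.8017 to 0.8012).

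**2. How often chance sets the model.** The article lists 5 demographic variables (age, education, marital status, occupation, gender), 4 comorbid diagnoses and 3 primary outcome scores: 5 + 4 + 3 = 12 tests. If the tests are independent (an assumption), the probability of at least one significant result is 1 − 0.95¹² = 46%. For the three baseline outcome scores alone it is 1 − 0.95³ = 14%. For the baseline value of any one outcome it is 5%, so in about 95% of realisations that value would not be used as a covariate for its own outcome.

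**3. Cost for the baseline outcome.** With complete data, a two-time-point mixed model with free baseline means is equivalent to a change-score test. The conditional rule is therefore a change-score test, replaced by ANCOVA when the baseline t test has p < 0.05.

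With equal SDs and baseline-post correlation r, a post-score effect d has standardised size:
- d / √(2(1 − r)) for the change score
- d / √(1 − r²) for ANCOVA

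Approximate power is Φ(size × √199 / 2 − 1.96). Example with d = 0.4 on the post score and r = 0.3:
- change score: 0.4 / √1.4 = 0.338, power 66%
- ANCOVA: 0.4 / √0.91 = 0.419, power 84%

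Simulation of the full rule (N = 199, simple 1:1 randomisation, alpha 0.05, d = 0.4 because f = 0.2 with two groups). The correlations are assumed, since the article gives none. Repeated runs agree to about one percentage point.

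| r (assumed) | Scale of d | Baseline always adjusted | Conditional rule | Difference, points |
|---|---|---|---|---|
| 0.3 | post score | 84% | 67% | 17 |
| 0.5 | post score | 90% | 82% | 8 |
| 0.7 | post score | 98% | 96% | 2 |
| 0.3 | change score | 93% | 81% | 12 |
| 0.5 | change score | 90% | 81% | 9 |
| 0.7 | change score | 86% | 81% | 5 |

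Under the null, the conditional rule rejects in about 4.0, 4.3 and 4.6% of trials at r = 0.3, 0.5 and 0.7.

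**4. The two covariate sets side by side.**

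| | Data analysis plan | Sample size |
|---|---|---|
| Entry rule | only if the baseline test is significant | fixed |
| Baseline outcome | conditional | not listed |
| Expectancy, acceptability | not listed | listed, no time point |

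**5. Which acceptability value?** If the post-intervention value is meant, Table 2 gives none for the waitlist arm at the primary time point, so it cannot serve in the between-arm comparison. It would also be affected by treatment. If the baseline value is meant, it exists in both arms but rates a treatment that nobody has yet received. For expectancy a baseline score is natural and usable. A post-intervention score meets the same obstacle as acceptability.

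**The case against.** The best case for the plan has four parts, and each limits the point.

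- **Baseline is not ignored.** The response is change from baseline, so the baseline score is already in the model. The change-score test is valid under randomisation. This stands: only the use of baseline as an additional covariate is conditional, and the issue is efficiency.
- **The planned power is met on one reading.** Sample size describes f = 0.2 as a difference in change. On that scale the conditional rule gives about 81% at every correlation tried, so what is lost is a gain that could have been had. It falls below 80% only if d is on the post score and the correlation is low (67% at 0.3). This also stands.
- **No excess of false positives.** The test level errs on the conservative side.
- **The sample size is not wrong.** 199 and 285 hold whichever covariate list is used.

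Two stronger readings are tempting. A reader might infer that the plan adjusts for acceptability measured after treatment. The documents do not support that: Sample size gives no time point, Table 2 also marks acceptability at baseline in both arms, and the Data analysis plan does not list it as a covariate. A reader might also infer from the Blinding section ("Statistical analyses will be carried out by a researcher blind to the study protocol") that the analyst is free to choose the model. That sentence does not say who chooses covariates, and the rule in the Data analysis plan is mechanical, so nothing here rests on it.

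What the objection does not remove is the selection rule itself, or the mismatch between the two sections.

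**Conclusion.** The point holds as a matter of efficiency and pre-specification. The Data analysis plan lets chance baseline results determine the covariates of the primary model, and the Sample size section describes a different model containing two secondary outcomes with unstated timing.

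Compared with always adjusting for baseline, the conditional rule gives up about 2 to 17 points of power if d = 0.4 is on the post score, and about 5 to 12 points if it is on the change score. These figures rest on N = 199, complete data, equal SDs, alpha 0.05 per outcome and assumed correlations of 0.3 to 0.7. They model only the decision about the baseline outcome, not the other covariates.

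Bias, inflated type I error and a wrong sample size are not shown.

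**What to change.** In the Data analysis plan, replace the covariate sentence. State that each primary model always includes the baseline value of its own outcome, either by ANCOVA or by a mixed model with a common baseline mean in the two arms, plus a short list of pre-randomisation covariates named in advance by the sponsor. State that no covariate is selected by a baseline test. Drop the balance tests and describe balance only.

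In the Sample size section, use the same list. Remove acceptability and any expectancy score taken after randomisation. If baseline expectancy is kept, say that the baseline measurement is meant.

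The cost is wording. The data are already in the assessment schedule, and 199 and 285 do not change. As recruitment has ended, the list should be fixed before outcomes are examined by arm.

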## Objectives

This paper describes the protocol for a two-arm parallel RCT study that compares the efficacy of a smartphone-based self-help CBT-I with a waitlist control group in treating people with MDD and insomnia in Hong Kong. It is hypothesized that, after the intervention, participants in the CBT-I condition will report a greater decrease in poor sleep quality, depression severity, and insomnia severity than those in the waitlist control condition. It is also hypothesized that the reduction in poor sleep quality, depression severity, and insomnia severity observed in the CBT-I condition will be maintained at 6-week follow-up. Furthermore, it is hypothesized that participants in the waitlist control condition will report a significant decrease in poor sleep quality, depression severity, and insomnia severity after receiving CBT-I.

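### The hypothesis that CBT-I gains are maintained at 6-week follow-up is matched only to a paired t test of no change, which cannot support it

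*Protocol article*

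**What the plan says.** The Objectives section of the protocol article states three hypotheses. The first is a greater decrease with CBT-I than on the waitlist after the intervention. The second is that the reduction "observed in the CBT-I condition will be maintained at 6-week follow-up". The third is that "participants in the waitlist control condition will report a significant decrease in poor sleep quality, depression severity, and insomnia severity after receiving CBT-I".

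The Data analysis plan assigns the mixed model to between-condition differences "in the primary outcome changes in sleep quality, insomnia, and depression severity from baseline to post-intervention assessments", so as described that model stops at post-intervention. For the next interval it names paired t tests on primary outcomes, subjective health and anxiety "obtained at post-intervention and 6-week follow-up separately for each condition". It adds: "All comparisons are planned with a 5% two-sided significance level", and then "Bonferroni adjustment will be applied", without giving the number of tests.

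The Participant timeline section says: "The waitlist control participants start CBT-I (equivalent to that of the CBT-I group) immediately after completing the post-intervention assessment". In Table 2, post-intervention is week 7 and follow-up is week 13.

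**The concern.** The null hypothesis of a paired t test between post-intervention and follow-up is that the mean did not change. Rejection shows a change, for better or worse. Non-rejection shows only that the data did not settle the matter. The second hypothesis, that nothing important was lost, is close to this null. Unless patients go on improving, a non-significant p value is the only result of the named test that could be offered in its support.

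This turns the usual safeguards round. Attrition, noisy measurement and a Bonferroni correction all make non-significance more likely, and so all make a reading of maintenance easier. The sample size gives no protection, because it was set for the between-arm change from baseline to post-intervention. A partial relapse in depression, one of the three primary outcomes, could be reported as a lasting benefit.

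A lesser matter concerns the waitlist arm. It is treated from week 7, so its change from week 7 to week 13 has no untreated comparison.

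**Working it through.** **The plan's own figure.** The Sample size section gives f = 0.2 (d = 2f = 0.4 for two equal groups), alpha 0.05, power 80% and 12 covariates. With a noncentral F, df1 = 1, df2 = N - 2 - 12 and lambda = f² × N, N = 199 gives df2 = 185, lambda = 0.04 × 199 = 7.96 and power 0.801. Attrition: 199 / 0.70 = 284.3, so 285. Both stated figures reproduce. They concern the baseline to post-intervention comparison only.

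**Inputs for the paired test in the CBT-I arm.**
- n: 199/2, about 100 (the number left after the planned attrition), and 285/2, about 142 (all randomised). The plan imputes missing values for all randomised participants. Imputation does not restore all lost information, so 142 is the optimistic end.
- True loss between post-intervention and follow-up: 0.2 SD (half of d = 0.4); 0.175 SD (half of the cited depression effect, g = 0.35); 0.395 SD (half of the cited insomnia effect, g = 0.79).
- Correlation rho between the two scores: not in the document; assumed 0.5 to 0.7.
- Bonferroni divisor: not in the document; assumed 3, one for each primary outcome, giving alpha = 0.05/3 = 0.0167.

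**Formula.** dz = loss / √(2(1 - rho)); noncentrality = dz × √n; chance of a miss = 1 - power of the two-sided paired t test (noncentral t, n - 1 df).

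Worked case: loss 0.2, rho 0.6, n = 100. dz = 0.2/√0.8 = 0.224 and noncentrality = 2.24. The loss is missed 40% of the time at 5% and 58% at 0.0167.

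| True loss | n | Missed at 5% (rho 0.7 to 0.5) | Missed at 0.0167 (rho 0.7 to 0.5) |
|---|---|---|---|
| 0.175 SD | 100 | 39-59% | 57-75% |
| 0.175 SD | 142 | 24-46% | 39-63% |
| 0.2 SD | 100 | 28-49% | 44-66% |
| 0.2 SD | 142 | 14-34% | 26-51% |
| 0.395 SD | 100 | under 3% | under 7% |
| 0.395 SD | 142 | under 1% | under 2% |

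In every row the stricter level raises the chance that a real loss goes unseen, and the smaller n does the same.

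**What a margin would cost.** Maintenance is declared if the 95% confidence limit for worsening lies within margin m (one-sided 0.025). With no true loss, power = Φ(m√n / √(2(1 - rho)) - 1.96). For an illustrative m = 0.2 SD:
- n = 100: Φ(2.00 - 1.96) = 52% at rho 0.5; Φ(2.58 - 1.96) = 73% at rho 0.7.
- n = 142: Φ(2.38 - 1.96) = 66% at rho 0.5; Φ(3.08 - 1.96) = 87% at rho 0.7.

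**The waitlist arm.** The third hypothesis is a within-arm decrease, and the paired test addresses exactly that. It cannot show the cause. A non-specific improvement of 0.2 SD, with no treatment effect at all, would be significant in 51-73% of trials at n = 100, alpha 0.05 and rho 0.5 to 0.7.

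**The case against.** Nowhere does the protocol say that a non-significant result will count as maintenance. That is correct: it is an inference from the hypothesis and the only test named for it. It is also fair that a condensed article may leave a numerical margin to a fuller document. The point therefore does not rest on the missing margin. It rests on the stated pairing of a no-loss hypothesis with a test of no change.

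A second objection is that the paired analysis is not itself at fault, since it also yields a confidence interval for the change. This stands. The decision rule needs changing; the test statistic need not.

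A third is that the size depends on assumptions and is small for insomnia. This also stands, which is why ranges are given and why the point matters mainly for losses of about 0.2 SD or less.

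A reader might go further and infer that the planned tests can answer neither of the two later hypotheses, or that the plan presents the waitlist's change as a controlled treatment effect. The document supports neither reading. The third hypothesis claims only a within-arm decrease, and the comparison with no treatment is made by the randomised baseline to post-intervention contrast. The lack of an untreated arm after week 7 follows from the waitlist design, chosen partly so that everyone is eventually treated, and no change of test cures it.

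**Conclusion.** The point holds for one hypothesis of three. The test named for maintenance can contradict it but cannot support it, and low information favours the claim. On the assumptions above, a true loss of half the planned effect goes undetected in 14-49% of trials at 5%, or 26-66% with a Bonferroni divisor of 3. A loss of half the cited insomnia effect goes undetected in less than 3% at 5%. The waitlist test matches its hypothesis, and only the labelling of its result needs attention. The main efficacy comparison and the sample size are untouched. This should be corrected, but it does not threaten the trial's primary conclusion.

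**What to change.** For each primary outcome, report the CBT-I arm's change from post-intervention to follow-up with a 95% confidence interval, either from a mixed model extended to all three time points or from the paired analysis. Claim maintenance only if the limit for worsening lies within a margin that the sponsor fixes and justifies before analysis. State that a non-significant difference alone will not be called maintenance.

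Label the waitlist's post-intervention to follow-up change as uncontrolled, non-randomised pre-post evidence. A contrast with that arm's own change while waiting is optional. It remains confounded by time and by regression to the mean: patients were selected on raised ISI and PHQ-9 scores, so regression should fall mainly in the first interval.

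The cost is a change of analysis wording, with no new data. The drawback is that maintenance becomes harder to claim: with the illustrative 0.2 SD margin and no true loss, the chance of showing it is about 52-73% at n = 100 and 66-87% at n = 142.
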